# The efficacy and safety of *Sipjeondaebo-tang* in Korean patients with cold hypersensitivity in the hands and feet: a protocol for a pilot, randomized, double-blind, placebo-controlled, parallel-group clinical trial

**DOI:** 10.1186/s13063-019-3286-7

**Published:** 2019-04-15

**Keywords:** Herbal medicine, Cold hypersensitivity, *Sipjeondaebo-tang*, Cold intolerance

## Abstract

**Background:**

Cold hypersensitivity in the hands and feet (CHHF) is frequent in Asian countries including Korea. The quality of life can be degraded by the symptoms of CHHF. In particular, gynecological disorders such as menstrual pain, infertility, leucorrhea, and irregular bleeding may be related to CHHF. *Sipjeondaebo-tang* (SDT) is widely used in the treatment of various diseases including CHHF by balancing Yin and Yang, restoring the deterioration of physiological function, and improving immunity. However, the efficacy of SDT in the treatment of CHHF has not been assessed in clinical trials. Therefore, we aimed to investigate the feasibility of a full randomized clinical trial of SDT for the treatment of CHHF in Korean women through this trial.

**Methods:**

This study will be a pilot, randomized, double-blind, two-arm, placebo-controlled, parallel-group, multicenter clinical trial. Women aged 19–59 years who present with CHHF will be recruited from five university hospitals. A total of 60 subjects will be randomly assigned to a treatment group (SDT) or a placebo group at a 1:1 ratio. The subjects will receive 3 g of either SDT or placebo three times daily for 8 weeks. The primary outcome measures will be the Visual Analogue Scale scores of CHHF. The secondary outcome measures will be changes in body temperature in both the hands and the feet as measured using a thermometer and the Korean version of the World Health Organization Quality of Life Scale Abbreviated Version.

**Discussion:**

This will be the first trial to investigate the efficacy and safety of SDT in the treatment of CHHF. This study will provide basic clinical information regarding Korean herbal medicine treatment of CHHF and a clinical basis for designing a full randomized clinical trial.

**Trial registration:**

ClinicalTrials.gov, NCT03374345. Registered on 15 February 2018.

**Electronic supplementary material:**

The online version of this article (10.1186/s13063-019-3286-7) contains supplementary material, which is available to authorized users.

## Background

Cold hypersensitivity in the hands and feet (CHHF) is defined as a condition in which patients experience the sense of coldness in the hands and feet to a greater extent than do unaffected people in any environment, with worsening symptoms at lower temperatures [1]. Cold hypersensitivity is frequent in Asians, particularly among females. The ratio of females to males is about 3:2. [2]. Severely affected persons may feel uncomfortable when working with their hands, and the quality of life can deteriorate due to the discomfort of wearing socks or gloves in hot weather [3].

Studies have investigated the relationship between CHHF and diseases such as orthostatic hypotension [4], functional dyspepsia [5], and dysmenorrhea [6]. In particular, not only menstrual pain but also other gynecological disorders such as infertility, leucorrhea, and irregular bleeding may be related to CHHF according to Korean medicine [2]. The cause of CHHF might be related to various neurovascular, medical, psychosocial, environmental, and cultural factors [7]. However, the clear etiology of and appropriate treatment strategy for CHHF have not been identified, and current therapies are often associated with behavior modification [8]. Therefore, the establishment of effective treatment methods for CHHF is essential.

*Sipjeondaebo-tang* (SDT) is a frequently prescribed herbal formula in Korea, Japan, and China [9]. It is also called *Shi-Quan-Da-Bu-Tang* in China, and *Juzen-taiho-to* in Japan. SDT is used to treat both qi and blood deficiency syndrome by balancing Yin and Yang. It is also widely used in the treatment of chronic illnesses by restoring the deterioration of physiological function and improving immunity [10]. For example, SDT is clinically prescribed to treat anorexia, coldness of the hands and feet, weakness after illness, anemia, and night sweats [11]. Previous studies have suggested that SDT possesses a variety of biological properties including anti-cancer, anti-inflammatory, gastric protective action, and immune cell activation [12–15].

Although SDT is widely used in the treatment of various diseases including CHHF, no randomized clinical trial (RCT) has yet been performed to assess the clinical efficacy of SDT in the treatment of CHHF. Therefore, this randomized, placebo-controlled, double-blind trial aims to examine the feasibility of a full RCT of SDT for the treatment of CHHF in Korean female patients, and to evaluate the efficacy and safety of SDT.

## Methods

### Objectives

The general aim of this study is to evaluate the efficacy and safety of SDT in patients with CHHF.

The primary objective is to evaluate the efficacy of SDT by comparing the changes in VAS scores between the SDT and placebo groups after 8 weeks of administration.

The secondary objective is to assess the efficacy of SDT by comparing changes in body temperature (BT; thermometer measurement) and the Korean version of the World Health Organization Quality of Life Scale Abbreviated Version (WHOQOL-BREF) scores between the SDT and placebo groups.

### Study design and setting

This is a 12-week pilot, randomized, double-blind, two-arm, placebo-controlled, parallel-group, multicenter clinical trial that will be conducted in Gachon University Gil Korean Medical Hospital, Korean Medical Hospital of Sangji University, Semyung University Second Affiliated Korean Medical Hospital at Chungju, Kyung Hee University Korean Medical Center, and Kyung Hee University Korean Medicine Hospital at Gangdong in Korea.

A written informed consent will be obtained from each subject by the principal investigator (PI) or researcher after the subject has received sufficient explanation and a period of time in which to make a thoughtful decision. Each subject will be screened up to 7 days prior to randomization. Once they receive the trial subject identifier, they will be treated for 8 weeks and asked to visit the site every 4 weeks for safety and efficacy assessments. A follow-up visit will occur at 4 weeks after the end of the administration. The participants will be asked to return any unused investigational drugs at visit 3 and visit 4 in order to calculate drug compliance. During the trial, the participants will be prohibited from receiving other medications related to CHHF. The protocol design is based on the Consolidated Standards of Reporting Trials (CONSORT) guidelines and Standard Protocol Items: Recommendations for Interventional Trials (SPIRIT) checklist (see Additional file 1). Figure 1 presents a schematic flow diagram of the study.

**Fig. 1 Fig1:**
[figure not shown]
Participant timeline for the *Sipjeondaebo-tang* (SDT) study

### Participants

#### Inclusion criteria

The inclusion criteria are presented in Table 1. Participants must meet all of the following criteria.

**Table 1 Tab1:** Inclusion criteria of the *Sipjeondaebo-tang* study

Inclusion criterion	
1. Women aged 19–59 years who present with CHHF	
2. Individuals who meet the following definition and have at least one of the following symptoms:	
2.1. Definition: those who feel cold in the hands or feet and experience discomfort	
2.2.1. Symptoms of CHHF at a temperature at which most individuals do not feel cold	
2.2.2. Symptoms of excessive CHHF at a temperature that one can feel cold	
2.2.3. Those who have symptoms of CHHF that do not recover easily when moving from a cold to a warm environment	
3. Those with a Visual Analogue Scale score of ≥ 4 cm at the screening visit	
4. At the screening visit, those who have a thermal difference of ≥ 0.3 °C between the palm (PC8) and the upper arm (LU4) as measured by a thermometer after room temperature adjustment at 24 ± 2 °C for 10 min.	
5. Those who can be observed during the clinical trial	
6. Those who agree to participate and provide written informed consent	

*CHHF* cold hypersensitivity in the hands and feet

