#### Study schedule

The items to be measured at each visit are presented in Table 4.

**Table 4 Tab4:** Study schedule for the trial

	Screening	Treatment period			Follow-up
	Visit 1 (day − 7 to − 2)	Visit 2 (day 0)	Visit 3 (day 28 ± 3)	Visit 4 (day 56 ± 3)	Visit 5 (day 84 ± 3)
Informed consent	●				
Inclusion/exclusion criteria	●				
Randomization		●			
Drug compliance			●	●	
Vital signs	●	●	●	●	●
Body measurement^a^	●	●	●	●	●
Demographic, sociological, and gynecological information^b^	●				
Medical history^c^	●	●	●	●	●
General physical examination	●	●	●	●	●
Thermometer measurement^d^	●	●	●	●	●
Visual Analogue Scale	●	●	●	●	●
Adverse event monitoring			●	●	●
Pattern Identification Questionnaire	●				
WHOQOL-BREF		●		●	●
Laboratory tests^e^	●			●	
Chest X-ray scan and ECG	●				
Medication		●	●		
Blindness test				●	

*ECG* electrocardiogram, *WHOQOL-BREF* World Health Organization Quality of Life Scale Abbreviated Version

^a^Height and weight, but only weight for visit 2 and follow-up

^b^Age, job, digestion, exercise, smoking habit, drinking habit, sleep pattern, etc.

^c^Including general medical history and history related to cold hypersensitivity in the hands and feet

^d^Temperature measurement of both PC8 and LU4 at every visit and both ST32 and LR3 at visit 2

^e^Screening: hematological examination (white blood cells, red blood cells, hemoglobin, platelet), blood chemistry test (blood urea nitrogen, creatinine, aspartate aminotransferase, alanine aminotransferase, gamma-glutamyl transpeptidase, glucose), thyroid function test (free thyroxine, thyroid-stimulating hormone), urine test, pregnancy test (urine human chorionic gonadotropin). Visit 4: hematological examination (white blood cells, red blood cells, hemoglobin, platelet), blood chemistry test (blood urea nitrogen, creatinine, aspartate aminotransferase, alanine aminotransferase, gamma-glutamyl transpeptidase)

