### Outcome

#### Primary outcome measure

The change in the VAS score between visit 2 (baseline) and visit 4 (after treatment) will be used as the primary outcome measure. The mean difference between the change scores of the two groups will be calculated.

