#### Visual Analogue Scale

The VAS score (ranging from 0 cm as no coldness to 10 cm as the maximum coldness imaginable) will be used to assess the severity of CHHF. The VAS score will be measured at every visit.

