#### Sample size calculation

The change in the VAS score between visit 2 (baseline) and visit 4 (after treatment) will be used as the primary outcome measure. The hypotheses are as follows:H0: δ = Δ1 – Δ2 = 0H1: δ = Δ1 – Δ2 ≠ 0

where Δ1 is the average change in the VAS score between visit 4 and visit 2 in the SDT group, and Δ2 is the average change in the VAS score between visit 4 and visit 2 in the placebo group

Based on a similar study [17], the expected average VAS score difference in the SDT group is 11.85 (larger than 10, because in the study used as a reference a 100-mm VAS was applied to assess severity of CHHF, and the scores ranged from 0 to 100), and the standard deviation (SD) is estimated to be 15.255 using the pooled standard deviation formula. Considering a dropout rate of 13%, which is agreed among medical experts, we need to recruit 30 subjects per arm to calculate the treatment efficacy, and to offer the power calculation for a future large-scale RCT.

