### Statistical analysis

#### Efficacy assessment

For the efficacy assessment of this trial, both intention-to-treat (ITT) and per-protocol (PP) analyses will be performed. Missing data will be adjusted using the last-observation-carried-forward (LOCF) imputation method on ITT analysis. For the safety assessment of this trial, PP analysis will be conducted. The continuous variables will be expressed as the mean ± SD and the nominal variables will be reported as percentages. The ITT method will include all randomly assigned subjects, regardless of any protocol violations or study dropouts. The PP method will include only the subjects who have completed the 12-week study period without any major protocol violations and who have a compliance rate of ≥ 70%. The baseline characteristics will be compared by either a chi-square test for nominal variables or analysis of variance (ANOVA) for continuous variables. For the within-group analysis, the primary and secondary outcome variables will be assessed using a paired *t* test. The between-groups analysis after 8 weeks of administration will be performed using a repeated-measure ANOVA for the primary outcome variables, and a paired *t* test for the mean difference in the VAS score between the SDT group and the placebo group. As a secondary outcome variable, the mean differences in BT and WHOQOL-BREF scores between the groups will be analyzed using a repeated-measure ANOVA for BT and an ANOVA and post-hoc analysis for the WHOQOL-BREF scores. For all non-normal distribution data, a nonparametric statistical test will be performed. SPSS for windows version 23.0 (SPSS Inc., Chicago, IL, USA) will be used for statistical analysis. The statistical significance level will be set at *P* < 0.05.

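### The primary VAS comparison is an unadjusted change from visit 2; an ANCOVA on the two pre-dose VAS readings already collected would probably be more precise, mostly through visit 2

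*Protocol article*

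**What the plan says.** - **Two pre-dose readings.** Under Visual Analogue Scale: "The VAS score will be measured at every visit". Study design and setting says: "Each subject will be screened up to 7 days prior to randomization". Table 4 puts visit 1 at day −7 to −2 and visit 2 at day 0, and first lists medication at visit 2. Both readings therefore precede treatment.
- **Use of visit 1.** Table 1, item 3 admits "Those with a Visual Analogue Scale score of ≥ 4 cm at the screening visit". No other use of that reading is stated.
- **Endpoint.** The section that defines the main endpoint reads: "The change in the VAS score between visit 2 (baseline) and visit 4 (after treatment) will be used as the primary outcome measure". Under Sample size calculation, the hypotheses are written on the same change.
- **Between-group analysis.** Efficacy assessment names a repeated-measures ANOVA for the primary outcome and a t test on the mean VAS difference. It names no baseline covariate and does not list the visits that enter the ANOVA.

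**The concern.** The primary outcome is a single self-rating on each of two days. In a raw change score, all the day-to-day error of the visit 2 rating passes into the outcome. The change score also subtracts the whole baseline value, where a regression would subtract only the part that predicts week 8. Two pre-treatment readings are on the case report form, and the stated comparison adjusts for neither.

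What is at stake is precision, not bias. Both readings precede dosing and the 4 cm threshold acts alike in both arms, so adjusting for them cannot bias the SDT–placebo contrast. The trial is small and is meant to inform the planning of a full RCT, so a wider interval than the data require is worth avoiding.

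**Working it through.** **Inputs from the article (Sample size calculation, Efficacy assessment).** Difference: "the expected average VAS score difference in the SDT group is 11.85", on a 0–100 mm scale, read here as the between-arm difference in change. SD: "the standard deviation (SD) is estimated to be 15.255 using the pooled standard deviation formula", read here as the SD of the change. Two-sided hypothesis, with "The statistical significance level will be set at *P* < 0.05". Dropout 13%, 30 per arm. Power is not stated; 80% is assumed because it reproduces the stated number.

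**The plan's own figure.** n = 2 × [15.255 × (1.960 + 0.842) / 11.85]² = 26.02 per arm; 26.02 / 0.87 = 29.9, so 30. Evaluable: 30 × 0.87 = 26.1, about 26 per arm.

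**Power of the unadjusted change.** Noncentrality = 11.85 / (15.255 × √(2/26)) = 11.85 / 4.231 = 2.80 on 50 degrees of freedom, giving 78.4%.

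**Formulas for the alternatives.** Take the same VAS variance σ² at each visit, with correlations r12, r24 and r14 between visits 1–2, 2–4 and 1–4.

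- Raw change: 2σ²(1 − r24)
- ANCOVA on visit 2 only: σ²(1 − r24²), which is (1 + r24)/2 of the raw-change variance
- ANCOVA on both: σ²[1 − (r14² + r24² − 2·r12·r14·r24)/(1 − r12²)]
- Change from the mean of visits 1 and 2, relative to raw change: [(1 + r12)/2 + 1 − (r14 + r24)] / [2(1 − r24)]

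The article gives none of these correlations, so the values below are assumptions. Entries are variances relative to the raw change, before allowing for the entry threshold.

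| r12, r24, r14 | Visit 2 only | Both | Extra from visit 1 | Averaged baseline |
|---|---|---|---|---|
| 0.5, 0.5, 0.5 | 0.75 | 0.67 | 11% | 0.75 |
| 0.7, 0.7, 0.7 | 0.85 | 0.71 | 17% | 0.75 |
| 0.7, 0.5, 0.5 | 0.75 | 0.71 | 6% | 0.85 |
| 0.8, 0.5, 0.45 | 0.75 | 0.74 | 1% | 0.95 |
| 0.9, 0.5, 0.45 | 0.75 | 0.75 | 0% | 1.00 |
| 0.9, 0.5, 0.40 | 0.75 | 0.74 | 2% | 1.05 |
| 0.8, 0.6, 0.5 | 0.80 | 0.80 | 0% | 1.00 |

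First row, both covariates: 1 − (0.25 + 0.25 − 0.25)/0.75 = 0.667, against a raw-change variance of 2 × 0.5 = 1.

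**Entry threshold.** Simulation with visit 1 truncated at 40 mm, over 12 assumed correlation sets, gave 0.67–0.91 for both covariates. Visit 1's own increment was about 0–15%. The averaged baseline ran from about 0.73 to 1.04.

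**Power at 26 per arm, charging two degrees of freedom (48).** Ratio 0.67: SD = 15.255 × √0.67 = 12.49, power 92%. Ratio 0.75: SD 13.21, power 89%. Ratio 0.91: SD 14.55, power 82%.

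**Regression to the mean under averaging.** With an assumed mean of 5–7 cm and SD of 1.5–2 cm, averaging visit 1 into the baseline added about 0.00–0.25 cm of spurious within-arm improvement, because visit 1 is the reading selected on.

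**The case against.** A day-0 reading is an ordinary baseline, and the article defines it consistently. Covariates are often settled in an analysis plan that is not shown. The benefit rests on correlations the article does not give. If correlation decays with time so that r14 = r12 × r24, visit 1 adds nothing once visit 2 is in the model and costs a degree of freedom. By publication 50 of 60 participants had been recruited, so any change is an amendment.

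Much of this stands. Visit 2 as baseline is not a mistake, and visit 1's own contribution may be nil. What survives is that the article does name its between-group methods, and none adjusts for baseline. In every correlation set run, the ANCOVA with both readings had lower variance than the raw change.

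Four stronger readings are tempting and are not supported:

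- *The visit 1 reading is thrown away.* It sets eligibility, and because the visits in the repeated-measures ANOVA are not listed, the article does not prove that it is left out of that model.
- *A second baseline reading cuts the variance by 25% whatever the correlation.* That holds for an averaged baseline only if readings 2–7 days apart correlate no better than readings 8 weeks apart. In other cases averaging gains nothing or loses.
- *The SD passed to the full RCT is inflated.* If that trial uses the same unadjusted change, this SD is the right planning figure.
- *The sample size is wrong.* The stated 30 per arm reproduces at an assumed 80% power.

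**Conclusion.** The point holds as a worthwhile gain in precision, not as an error or a contradiction. The stated between-group comparison of VAS is unadjusted, although two pre-dose readings exist. Adjusting for both is expected to cut the variance by about 9–33% relative to the raw change, raising power at 26 per arm from 78% to about 82–92%. In most of the assumed sets the larger part comes from visit 2. Visit 1 adds about 0–15%, most when all visits are equally and strongly correlated and least when visits 1 and 2 are nearly interchangeable.

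These figures rest on assumed correlations of 0.4–0.9, equal variances across visits, and 15.255 being the SD of change. The 9% is not a guaranteed minimum: the visit 2 ratio (1 + r24)/2 approaches 1 as r24 does.

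**What to change.** For the between-group primary analysis, specify before unblinding an ANCOVA of visit 4 VAS with treatment group, visit 2 VAS and visit 1 VAS in the model. Using the visit 2 to visit 4 change as the response gives the same treatment estimate, so the endpoint need not be redefined. Keep that change as the endpoint and as the within-arm summary. Do not use the mean of visits 1 and 2 as baseline: it can lose precision and brings regression to the mean from the entry threshold into the within-arm figures.

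For planning the full RCT, report the SD of the unadjusted change, the ANCOVA residual SD and the observed between-visit correlations, so that the planning SD can match the analysis chosen.

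The cost is two degrees of freedom against the unadjusted test (50 to 48), or one against an ANCOVA on visit 2 alone, plus a short amendment to the analysis wording. No new data, visit or participant is needed. Recruitment was still open at publication and the database is to be locked only after the trial is completed, so there is time to fix this in advance.

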### Exclusion criteria

The exclusion criteria of the SDT trial are presented in Table 2. Applicants who meet any of these conditions cannot participate in this study.

**Table 2 Tab2:** Exclusion criteria of the trial

Exclusion criterion	
1. Patients receiving beta-blockers or calcium antagonists for the purpose of treatment of CHHF	
2. Patients with one or more ulcers or gangrene of the finger	
3. Those who have been diagnosed with hypothyroidism or prescribed thyroid medications	
4. Those who have been diagnosed with autoimmune diseases	
5. Those who have been diagnosed with carpal tunnel syndrome or have positive results on Phalen’s and Tinel’s tests	
6. Those who have been diagnosed with cervical disc herniation	
7. Those who have been diagnosed with diabetes mellitus	
8. Those receiving medicines that can affect the symptoms of CHHF, such as anticoagulants	
9. Those who present with CHHF due to postpartum or menopausal syndrome	
10. Those who present with a moderate level of liver dysfunction (AST and ALT levels of > 100 IU/L) or kidney dysfunction (creatinine level of > 2.0 mg/dl)	
11. Those who have behavior disorder, depression, anxiety, neurosis, or any other severe mental disorder	
12. Adult nonpregnant women with a hemoglobin level of < 7 g/dl and WBC count of > 11 cells × 10^9^ L	
13. Those whose mean SBP is ≥ 180 mmHg or DBP is ≥ 100 mmHg when measured twice	
14. Patients with an arrhythmia as determined by an electrocardiogram and requiring treatment, or with heart disease such as ischemic heart disease	
15. Alcohol or drug abusers	
16. Women who are pregnant (urine hCG positive), lactating women, and fertile women who have a pregnancy plan or do not consent to the proper method of contraception	
17. Those who have been diagnosed with a malignant tumor	
18. Those who are participating in other clinical trials	
19. Those who refuse to participate in clinical trials or provide written informed consent	
20. Those who cannot understand or speak Korean	
21. Those who are judged to be inappropriate for clinical trials by the researchers	

*ALT* alanine aminotransferase, *AST* aspartate aminotransferase, *CHHF* cold hypersensitivity in the hands and feet, *DBP* diastolic blood pressure, *hCG* human chorionic gonadotropin, *SBP* systolic blood pressure, *WBC* white blood cell

